### Baseline and follow up assessments

Assessments will be completed by a researcher and take place at baseline and 52 weeks post-randomisation. Demographic information will be collected at baseline e.g. grade, caseload size, year of qualification, previous physical health care education (MHNs) and diagnosis, age, post-code (patients). The following validated measures will be used at baseline and 52 weeks in both the HIP and TAU groups:

1. PCS and MCS of the SF36v2

2. EQ-5D

3. HRU (patient)

4. PHASe adapted

The following will be used at baseline and at 52 weeks in the HIP programme group only:

1. HRU: Health Service Use Questionnaire (nurse)

2. The QRISK^®^2

and in a sample of patients from the HIP Programme group after 12 months

1. HIP Audit Form

Feedback will be sought from a sample of HIP Programme group participants in the Patient Interviews, Nurse Focus Groups and Psychiatrist/GP telephone interviews after one year using the Patient Semi-structured Interview Schedule, the Nurse Focus Group Interview Schedule and the Psychiatrist/GP Telephone Interview Schedule.

### Description and core principles of the intervention

The HIP is a gender specific 27-item physical health risk assessment tool. The profile includes items on cardio-vascular risk factors such as BMI (body mass index), cholesterol, diet, smoking and exercise but also addresses other aspects of wellbeing such as sexual health and satisfaction, sleep, dental and eye health and breast, prostate and testicular self examination. Each of the 27 items are flagged either green (healthy) or red (not healthy). The HIP then directs nurses to evidence/guideline-based interventions for each of the red flagged items[43].

HIP training takes place in a 6 hour workshop delivered by JW, RG or MJ and will include: how to use the HIP; how to engage patients in health behaviour change and work with them to develop a patient specific health action plan. A HIP Manual will be provided. Competency in physical observation skills are expected of all MHNs employed in the NHS, assured through a continuing professional development process which will be signposted in the training, the HIP Manual and by the Team Leaders through the usual clinical supervision processes, if necessary.

### Definition of End of Study

#### Part 1

Date of the last 52-week visit for the last patient.

#### Part 2

Date of the last interview/focus group or date of the last patient HIP Audit visit, whichever occurs last.

## Analysis

### Description of Statistical Methods

The analysis and reporting of the trial will be undertaken in accordance with Consolidated Standards of Reporting Trials [CONSORT] [44,45]. Standard methods will be used to provide tabular and graphical summaries as appropriate for continuous and categorical variables. Primary and secondary outcomes will be compared between intervention and control groups using linear or logistic regression as appropriate including a random term to allow for nurse clusters. Further adjusted estimates will be calculated by including the baseline value of the outcome in these models. Where between group differences are observed in demographics or patient characteristics at baseline, terms representing these variables will also be included to obtain adjusted estimates of the intervention effect. The characteristics of the MHNs will be compared between groups. If differences occur these may be incorporated into a multilevel model structure. The latest available versions of the Statistical Package for the Social Sciences [SPSS] and Stata will be used for the analysis. It is not our intention to conduct any subgroup analyses.

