### Efficacy analysis

Efficacy of the intervention will be assessed by comparing the patient outcomes at 52 weeks between the two groups allowing for the clustering effect of the nurse. Further, adjusted estimates will be obtained by identifying baseline variables that differ between the two groups, which are related to the outcome and incorporating these into the analyses.

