### Inclusion in Analysis

An intention to treat (ITT) analysis will be performed. The ITT analysis set will comprise all patients who were randomised to a group at baseline (HIP Programme or TAU group), irrespective of any change to the other group over the course of the trial. This is the main analysis and will be used for evaluation of all endpoints. However, we acknowledge there may be attrition due to nurses leaving teams and where patients may be unavoidably switched to a nurse participant caseload in a group other than the one they were randomised to at baseline or to a MHN not in the study. To enable an evaluation of the effects of this on the primary outcome we will undertake and report a secondary per protocol [PP] analysis. HIP and non-HIP patients will be included in groups on an intention to treat basis. The primary analysis will include non-missing data only. However, where there is attrition at follow up the baseline characteristics of missing and non-missing values will be compared. Further, we will perform sensitivity analyses by (i) assuming zero change in scores and (ii) employing current multiple imputation techniques.

A per protocol analysis will also be performed. Per protocol will be defined as the participant remaining in the same arm of the study as at randomisation.

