The Medical Research Council recommend researchers pay attention to the interplay between development, feasibility, evaluation and implementation when designing complex health interventions[56]. In the development stage, initial piloting of the HIP was positive with mental health nurses, patients, psychiatrists and GPs reporting that it is acceptable, avoids duplication of work, enables previously unidentified physical comorbidities to be uncovered and improves care planning and interface communication. Clinical utility and acceptability were then established in an exploratory case series within a community MH service in Scotland[32].

To maximise success in the future implementation of the HIP we have included an education package to meet the individual and organisational needs of the staff most likely to be in contact with people with SMI. The cluster design with the MHN as the cluster has been adopted because the focus of the intervention depends on the training and adoption of the HIP by MHNs. In evaluating the success of our intervention, the HIP and the training package together [the HIP Programme], we will evaluate patient outcomes and conduct a process observation. This will allow us to report education outcomes (any change in nurse knowledge of and attitudes towards a physical healthcare role using the adapted PHASe [40]) in addition to our primary evaluation of effectiveness and cost effectiveness.

The primary end point of this proposed study, change in physical related quality of life, has meaning to patients, carers, practitioners and policy makers and will formally explore the clinical potential of the tool. We have a specific qualitative element to explore patient, practitioner and medical experience of the HIP. Qualitative and audit data will enable us to more fully test the acceptability of this approach and further refine it as necessary. The health economic element of the study will provide important information about the costs of disseminating this approach across the NHS in terms of any additional service costs and Quality Adjusted Life Years (QALYs). The evaluation of HIP trainees knowledge and attitude towards physical health post HIP training will inform future workforce training and implementation plans.

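### The plan leads with an unadjusted comparison of 52-week PCS and does not say which estimate decides the trial; making the already planned baseline-adjusted model primary would gain precision at no cost

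*Protocol article*

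**What the plan says.** Under Description of Statistical Methods, primary and secondary outcomes are compared between arms by "linear or logistic regression as appropriate including a random term to allow for nurse clusters". The next sentence brings in baseline: "Further adjusted estimates will be calculated by including the baseline value of the outcome in these models". Terms for patient characteristics seen to differ at baseline follow, and then nurse characteristics: "If differences occur these may be incorporated into a multilevel model structure".

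Efficacy analysis keeps the same order. Efficacy is "assessed by comparing the patient outcomes at 52 weeks between the two groups allowing for the clustering effect of the nurse", after which "adjusted estimates will be obtained by identifying baseline variables that differ between the two groups, which are related to the outcome".

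Inclusion in Analysis fixes the analysis set as intention to treat and adds: "The primary analysis will include non-missing data only". It does not say which of the estimates is primary.

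The Discussion describes the endpoint differently: "The primary end point of this proposed study, change in physical related quality of life".

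Baseline and follow up assessments lists PCS at baseline and 52 weeks in both arms. Informed Consent places baseline collection before any participant learns the allocation.

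**The concern.** Baseline PCS is collected in both arms before allocation is revealed, and it is an obvious candidate to predict 52-week PCS. The plan gives the lead to the estimate that leaves it out and places the more precise model second.

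That the unadjusted estimate leads has to be inferred from the word *further* and from a power calculation that uses the raw SD. Nothing labels it primary. The other adjusted estimates use covariates picked after baseline differences, and in one section their relation to outcome, have been seen. A reader of the results could therefore face several estimates with no stated rule for which one counts.

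Two things are at stake: precision in a trial with only 50 randomised units, and a primary result that is unambiguous before the data are seen.

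**Working it through.** **Inputs from Number of Participants:** 25 nurses per arm; 5 patients each, 4 after 20% attrition; SD 12; difference 6 points; ICC 0.1 or 0.2; two-sided alpha 0.05.

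**Assumed, not in the article:** the correlation r between baseline and 52-week PCS, shown over a range. It is taken as equal between and within nurses, with the ICC unchanged after adjustment.

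**1. The plan's own power**
- Design effect = 1 + (4 − 1) × ICC = 1.3 (ICC 0.1) or 1.6 (ICC 0.2).
- Effective n per arm = 100/1.3 = 76.9 or 100/1.6 = 62.5.
- SE = 12 × √(2/76.9) = 1.935 or 12 × √(2/62.5) = 2.147.
- Noncentrality = 6/SE = 3.10 or 2.80.
- Power, noncentral t with 48 df: 86.0% or 78.2%. The normal approximation gives 87.3% or 79.8%.

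This matches the stated 86% and nearly 80%. The raw SD is used without any baseline correlation, so the trial was sized on the unadjusted comparison.

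**2. With baseline PCS in the model**

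The SD becomes 12 × √(1 − r²), with 47 df. The variance falls to 0.91, 0.75 or 0.51 of the unadjusted value at r = 0.3, 0.5 or 0.7.

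| Analysis | Power, ICC 0.1 | Power, ICC 0.2 |
|---|---|---|
| Unadjusted 52-week PCS | 86.0% | 78.2% |
| Baseline-adjusted, r = 0.3 | 88.9% | 81.9% |
| Baseline-adjusted, r = 0.5 | 93.9% | 88.5% |
| Baseline-adjusted, r = 0.7 | 98.9% | 96.9% |

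**3. Confidence interval half-width at r = 0.6, ICC 0.1**
- Unadjusted: 2.011 × 1.935 = 3.89 points.
- Adjusted: SE = 1.935 × √(1 − 0.36) = 1.548, so 2.012 × 1.548 = 3.11 points.

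**4. Chance baseline imbalance**
- SD of the between-arm difference in baseline PCS among 125 patients per arm = 12 × √(2 × (1 + 4 × ICC)/125) = 1.80 (ICC 0.1) or 2.04 (ICC 0.2).
- About r times any such imbalance carries into the unadjusted estimate. At r = 0.5, an imbalance of one SD shifts it by about 0.9 to 1.0 points.

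**5. Does the Discussion's wording matter?**

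An unadjusted change score would have SD 12 × √(2(1 − r)). At r = 0.3, 0.5 and 0.7 its power is 72.8, 86.0 and 97.5% (ICC 0.1), or 63.9, 78.2 and 94.2% (ICC 0.2). It does worse than the 52-week score below r = 0.5 and better above it, so the two are not interchangeable. Once baseline PCS is a covariate, modelling the score or the change gives the same treatment effect, and the difference in wording has no effect on the result.

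**The case against.** The best defence is that the analysis is sound as written. The model recommended here is already planned, the unadjusted comparison is valid, and the power was calculated for that comparison and reproduces. The whole gain rests on a correlation the article does not report. All of this stands, and it is why the point is an improvement and not an error. The gain does not need any particular r, though: any non-zero correlation favours adjustment, apart from the negligible cost of one degree of freedom.

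A second defence is that naming the headline model is commonly left to a statistical analysis plan, which is not shown. That would answer a complaint about silence. Here the article states its models and their order, and the order puts the less precise one first.

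Several stronger readings are tempting, but the document does not support them:

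- *Baseline PCS is ignored.* It is used, in the further estimates; only its rank is at issue.
- *A change-score analysis competes for primary.* None is planned. The phrase is Discussion prose, and the analysis sections consistently refer to outcomes at 52 weeks.
- *Using non-missing data only makes the unadjusted estimate biased whenever drop-out depends on baseline health.* If that dependence is the same in both arms and the effect does not vary with baseline, the difference in means stays unbiased. Bias needs dependence that differs by arm, or an effect that varies with baseline, and the article gives no reason to expect either. It also plans a comparison of missing and non-missing patients, a zero-change analysis and multiple imputation.
- *A chance imbalance passes in full into the result.* Only about r times it does, and that variation is already in the standard error and the stated power.

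**Conclusion.** The point holds as a should-fix. The plan leads with a valid but less precise estimate and never says which estimate decides the trial. Over r = 0.3 to 0.7, adjustment adds about 3 to 13 percentage points of power at ICC 0.1 (86.0% to 88.9–98.9%) and about 4 to 19 at ICC 0.2 (78.2% to 81.9–96.9%). At ICC 0.2 the unadjusted analysis is just under 80%, and adjustment exceeds 80% even at r = 0.3.

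These sizes depend on the assumed r, on its being equal between and within nurses, and on an unchanged ICC; the direction needs only a non-zero r. With completers only, adjustment has one further benefit: it protects against drop-out that depends on baseline PCS differently by arm, provided drop-out depends on nothing beyond baseline PCS and arm and the linear model holds. The figures do not show that the trial is underpowered or its planned comparison invalid.

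**What to change.** In Description of Statistical Methods and Efficacy analysis, name a single primary analysis: a linear mixed model of 52-week PCS on arm and baseline PCS, with a nurse random intercept. Use the same form for MCS and EQ-5D. Report the unadjusted comparison, and any estimate with covariates chosen because of observed imbalance, as supportive.

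In the Discussion, describe the endpoint as PCS at 52 weeks adjusted for baseline, or note that with baseline in the model the score and the change give the same treatment effect.

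The cost is a sentence or two of text. No data, visits or patients are added, and the stated sample size can stand, since it is conservative for the adjusted model under the assumptions above.

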### Baseline analyses

To assess external generalisability, demographic and clinical characteristics of patient participants invited to participate in the study at baseline will be compared with participants who are subsequently randomised and participants who are screened but not randomised. The specific criteria by which participants are excluded from randomisation will be tabulated. Baseline comparability will be assessed using descriptive statistics only.

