### Number of Participants

#### Part 1

A sample size of 50 MHNs will be sought (25 in the HIP and 25 in the TAU group), with 5 patients each resulting in an overall sample size of 250 patients (125 in the HIP and 125 in the TAU group). Based on a standard deviation of about 12 points as found in MOS patients (adults in various settings with SMI in the US), a difference in means between intervention and TAU of 6 points in the SF36v2 PCS subscale is equivalent to a medium effect size. The proposed sample size gives a power of 86% to detect this if an intraclass correlation of 0.1 is assumed and nearly 80% if an intraclass correlation of 0.2 is assumed using a 2-sided significance level of 0.05 and allowing for an estimated 20% attrition rate i.e. 1 patient per nurse.

All MHNs in the HIP and TAU groups will be invited to participate in the online PHASe adapted at baseline and one year. Response rates will be reported. All patients remaining the HIP Group at one year will provide data for evaluation of any change in their QRISK^®^2 Scores. Retention rates will be reported.

#### Part 2

The patient records of the 36 randomly selected patients from the HIP Programme Group will be audited using the HIP Audit Form. We will purposefully recruit from the HIP Group (on completion of Part 1) 10 patients to participate in the Patient Semi-structured Interviews, 10 nurses to participate in a Focus Group (per Trust study site) 5 psychiatrists and 5 GPs to participate in the telephone interviews. (30 in total). The aim of this element of the project is to elicit general feedback that will help in refining and further developing the HIP. The qualitative literature indicates that this number of data collection interviews per homogenous professional or patient group should allow us to reach saturation of themes [46].

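### Covariates for the further adjusted estimates are chosen by observed baseline imbalance, under conditions that differ between sections, and no model is named as primary

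*Protocol article*

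**What the plan says.** The Description of Statistical Methods builds the comparison in layers.

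- The base is "linear or logistic regression as appropriate including a random term to allow for nurse clusters".
- Next comes the baseline outcome: "Further adjusted estimates will be calculated by including the baseline value of the outcome in these models".
- Then come patient characteristics, selected by imbalance: "Where between group differences are observed in demographics or patient characteristics at baseline, terms representing these variables will also be included".
- For characteristics of the nurses, the wording is optional: "If differences occur these may be incorporated into a multilevel model structure".

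The Efficacy analysis section states the selection again with a second condition: "adjusted estimates will be obtained by identifying baseline variables that differ between the two groups, which are related to the outcome". The Baseline analyses section says how a difference is judged: "Baseline comparability will be assessed using descriptive statistics only". The article gives no cut-off for a difference and no criterion for relation to the outcome. The Inclusion in Analysis section says which analysis set is the main one, but no section says which of the layered models carries the inference.

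**The concern.** Imbalance between randomised arms says nothing about whether a variable predicts the outcome. Using it to select covariates has three consequences for the further adjusted estimates.

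- The covariate set, and so the estimate, varies with chance and with whoever decides what counts as a difference.
- A strong predictor that happens to be balanced is left out, and the precision it would have given is lost.
- The model standard error takes the selected set as given, so it is not exactly calibrated.

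The sections also disagree about the selection rule. A later analysis plan could not follow both as written, so this is more than detail left for that plan. Because no model is ranked first, one of these estimates could be put forward as the main result.

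**Working it through.** **1. The plan's own figure.** Inputs from Number of Participants: 25 nurses per arm, 4 of 5 patients analysed per nurse, difference 6, SD 12, two-sided 0.05. Effective n per arm = 25 × 4 / (1 + 3 × ICC). Power = Φ(0.5 × √(n/2) − 1.96).

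- ICC 0.1: n = 100/1.3 = 76.9; power 87.3% (86.0% with a noncentral t on 48 df). Stated: 86%.
- ICC 0.2: n = 100/1.6 = 62.5; power 79.8% (78.2% with t). Stated: nearly 80%.

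The figures reproduce. They use no covariates, so this point does not change them.

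**2. The rules side by side.**

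| Patient variable | Description of Statistical Methods | Efficacy analysis |
|---|---|---|
| Differs, unrelated to outcome | included | left out |
| Differs, related to outcome | included | included |
| Balanced, related to outcome | left out | left out |

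The first row is the disagreement. The third row is the loss common to both.

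**3. Is the imbalance chance?** Under Randomisation, a nurse is randomised once five patients are recruited or after six weeks, and no patient is added afterwards. Under Informed Consent, baseline data are collected before the allocation is revealed to any participant. So differences in patient characteristics, and in fixed nurse characteristics such as grade, arise by chance. The adapted nurse attitude survey is an exception in timing: it is completed once nurses are randomised.

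**4. How often would a rule be triggered?** For one covariate with 125 patients per arm, the standard error of the standardised difference is √(2/n). Here n = 125 without clustering, or 125/1.4 = 89.3 with a covariate ICC of 0.1 (assumed). The cut-offs, and a count of 8 independent candidates, are also assumptions.

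| Cut-off | One covariate | At least one of 8: 1 − (1 − p)^8 | Expected number of 8 |
|---|---|---|---|
| 0.1 | 0.43 to 0.50 | 99% to over 99% | 3.4 to 4.0 |
| 0.2 | 0.11 to 0.18 | 62% to 80% | 0.9 to 1.5 |

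**5. What does the selection do to the estimate?** 4,000 trials were simulated with no effect: 25 nurses × 4 patients per arm, SD 12, residual ICC 0.1, and baseline score correlated 0.5 with outcome. There were 8 candidate covariates, 4 of them prognostic. Apart from the nurse and patient counts and the SD, the inputs are assumed; ICC 0.1 is one of the plan's two values. All models below include the baseline outcome.

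| Covariates | Empirical SE | Mean model SE | Type I error |
|---|---|---|---|
| Baseline outcome only | 1.65 | 1.68 | 4.2% |
| Difference > 0.1 | 1.53 | 1.61 | 3.6% |
| Difference > 0.2 | 1.56 | 1.66 | 3.3% |
| Difference at p < 0.05 | 1.61 | 1.68 | 3.7% |
| Difference > 0.1 and related to outcome | 1.52 | 1.60 | 3.5% |
| Four prognostic covariates fixed in advance | 1.50 | 1.51 | 4.5% |

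- Across the four imbalance rules, estimates within a trial differed by a median of 0.56 points (95th percentile 1.3). As a share of the 6-point target: 0.56/6 = 9% and 1.3/6 = 22%.
- The two sections' rules at the same 0.1 cut-off differed by a median of 0.16 points (95th percentile 0.61), or 3% and 10% of the target.
- Against the fixed set, the empirical SE is 1.52/1.50 to 1.61/1.50, about 1% to 7% larger.
- Taking whichever of the four rules reached significance gave a type I error of about 5.4%.

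Two limits apply. The fits hold the ICC at 0.1 instead of estimating it, and the baseline-only model, which involves no selection, is itself slightly conservative. So not all of the gap between model and empirical SE is due to selection. The fixed set also contains exactly the prognostic covariates, which favours it.

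**The case against.** The strongest reply is that the main comparison is untouched. The Efficacy analysis section opens by comparing 52-week outcomes with allowance for nurse clustering, and imbalance enters only in what is called further adjustment. The baseline outcome, usually the strongest predictor, is included whatever the imbalance. The Efficacy wording can be read as a refinement of the Methods wording, and the nurse rule concerns a different level, so it is discretion more than contradiction. The numerical gap between the two rules is small.

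Most of this stands and limits the weight of the point. It does not remove it: the rules still select by chance, they still differ, and no sentence ranks the models.

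A reader might infer more than the documents support:

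- **That type I error is inflated.** For any single rule the simulation shows the opposite, mildly.
- **That the covariates are chosen after seeing outcomes by arm.** The Methods rule uses baseline data only. The Efficacy rule does not say that relation to outcome is judged from trial data by arm.
- **That baseline significance tests will drive the choice.** The Baseline analyses section plans descriptive statistics only, so a false-positive rate at p < 0.05 does not describe this plan. That cut-off above is only one possible reading of a difference.

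**Conclusion.** The point holds for the further adjusted estimates and should be corrected. They depend on chance imbalance and on which rule is applied, and they omit balanced prognostic variables. Their standard errors are slightly miscalibrated, on the conservative side in simulation.

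The size is modest: a median spread of 0.56 points across four readings, 0.16 points between the two sections' rules at one cut-off, and an SE about 1% to 7% larger than with a well-chosen fixed set. These figures rest on the assumed number, strength and clustering of covariates, since the documents give none. The textual disagreement and the argument that imbalance is chance do not rest on them.

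The estimate with only the nurse random term, the estimate adding the baseline outcome, and the stated power are unaffected. It would go too far to say that the trial's main answer is compromised. The open matter is that the text leaves unranked which estimate is that answer.

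**What to change.** Replace the imbalance-driven rules in Description of Statistical Methods and Efficacy analysis with one statement used in both places:

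- Fix one covariate set before any outcome data are seen, chosen on expected prognostic value regardless of observed balance. It would hold the baseline value of the outcome plus a short list from data already collected or known, such as age, diagnosis, Trust and nurse grade. The documents do not show that these predict the physical component score, so the investigators should confirm the list.
- Fit it with a nurse random intercept and name this baseline-adjusted model as the primary analysis. Report the estimate with only the nurse random term beside it.
- Keep the baseline tables descriptive. If imbalance-driven adjustment is retained, label it as a sensitivity analysis and give it one rule.

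The cost is wording and a few degrees of freedom. At nurse level, Trust takes 1 and grade (bands 5 to 7) takes 2, so about 3 of the 50 − 2 = 48 available. No new data are needed, and the sample size is unchanged.
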